## 8.2 Statistical methods

A Statistical Analysis Plan describing all details of the analyses to be performed will be prepared by the study statistician and approved by the sponsor prior to the start of statistical analysis. The recommendations of the ICH E9 Note for Guidance on Statistical Principles for Clinical Trials (CPMP/ICH/363/96, 1998) will be taken into account.

The primary endpoint will be subjected to a confirmatory analysis. All secondary and safety parameters will be evaluated and reported descriptively.

All individual data as well as results of statistical analyses – whether explicitly discussed in the following sections or not – will be presented in individual subject data listings and statistical summary tables.

Continuous variables will be summarised using the following standard descriptive summary statistics: number of observations, arithmetic mean, standard deviation, minimum, lower quartile, median, upper quartile, maximum. In addition, geometric mean and coefficient of variation derived from log-normally distributed data will be calculated for serum concentrations. Categorical data will be described using absolute and relative frequencies.

A more detailed elaboration of the principal statistical features stated in this protocol will be provided in the statistical analysis plan, which will be finalized prior to unblinding of the database. The statistical analysis plan will take into account any amendment to the study protocol.

### 8.2.1 Populations

The following data sets will be analysed:

- Full-analysis set:

All randomised patients who received at least one dose of study medication will be included in the all patients treated set.

- Per-protocol analysis set:

The per protocol analysis set will consist of all patients in the full analysis set without any major protocol violations. Patients with major protocol violations will be excluded from the per-protocol analysis. The classification of major and minor protocol deviations and the resulting definition of analysis sets will be performed prior to the final analysis and will be approved by the sponsor.

All analyses with respect to safety and tolerance will be performed for the full-analysis set. All efficacy analyses will be conducted for the full-analysis set and for the per-protocol analysis set. The primary data set for the efficacy analysis will be the full-analysis set.

A more detailed description of the criteria used for data sort out will be included in the statistical analysis plan before start of the evaluations prior to unblinding the treatment allocation.

### 8.2.2 Background and demographic characteristics

Assessments made at the screening (V0) and randomization visit V1 will be summarised by treatment group and overall. These assessments will include demographic characteristics and other relevant parameters (such as medical history and physical examination). By-treatment summaries will serve to identify any imbalances between the treatment groups before start of active treatment.

Previous / concurrent diseases will be coded and presented according to the MedDRA terminology.

Summary tables will be provided for the the full-analysis set and for the per-protocol analysis set by means of descriptive statistics and frequency tables where appropriate.

### 8.2.3 Study medication

Compliance with respect to study medication will be computed based on the available data of the number of dispensed and returned study medication and the number of days the patient should have taken medication (dispensing intervals).

### 8.2.4 Concomitant therapy

Concomitant medications will be tabulated by generic drug name and Anatomical Therapeutic Chemical (ATC) code for each treatment group.

### 8.2.5 Efficacy evaluation

The primary objective of the study is to demonstrate the superiority of the test treatment compared to the standard treatment in terms of survival.

The study will be conducted according to a two-stage group sequential test design with possible sample size adaptation after the planned interim analysis. The overall type-I-error rate is set at  $\alpha = 0.025$  (one-sided).

The following null hypothesis  $H_0$  will be tested against the alternative hypothesis  $H_A$  ( $\alpha = 0.025$ , one-sided):

$$H_0: \lambda_2 / \lambda_1 \geq 1$$

$$H_A: \lambda_2 / \lambda_1 < 1$$

where  $\lambda_2 / \lambda_1$  is the hazard ratio,  $\lambda_1$  denotes the hazard in the standard group and  $\lambda_2$  in the test group. The hazard ratio is assumed to be constant across time.

The null hypothesis will be tested using the log-rank test.

The first interim analysis will be conducted after observation of a total of 31 deaths. The null hypothesis will be rejected at the first interim analysis if the calculated test statistic exceeds the critical value 2.797. In this case, the study may be stopped. If the null hypothesis will not be rejected, the study may be continued until the pre-specified number of 61 deaths (accumulated number of deaths) or a recalculated number of deaths based on the effect size estimation of the first interim analysis were observed.

Data from all subjects will be considered when calculating the second stage log-rank test statistic. At the final (second) analysis, the null hypothesis will be rejected if the calculated inverse normal test statistic exceeds the critical value 1.977.

This procedure preserves the overall (experiment-wise) type I error rate of  $\alpha = 0.025$  in a strong sense.

For estimating the treatment effect, the hazard ratio and the corresponding two-sided 95% repeated confidence interval will be provided.

All other group comparisons are hypothesis generating in nature, i.e., p-values resulting from these statistical tests will be interpreted in the exploratory sense.

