## **6.10 Randomisation and unblinding procedures**

### **6.10.1 Randomisation**

At the screening visit (V0), each patient will receive the next consecutive screening number from a block of screening numbers according to their stratum (bulbar onset vs. spinal onset). Patients will be assigned to the bulbar or spinal stratum according to the location of the earliest experienced ALS symptom (defined by the first muscle weakness, or in the case of bulbar onset, by the presence of dysarthria and/or dysphagia). In the case of a patient with simultaneous onset of spinal and bulbar symptoms, onset will be defined as bulbar. Cervical and respiratory onsets are stratified to the spinal-onset stratum. This stratum assignment must be consistent with the diagnosis and clinical assessment (i.e., maximum score on bulbar scale and low score on manual muscle testing would contradict the assignment to bulbar stratum).

At the randomization visit (V1), each patient eligible for study participation will receive the next consecutive randomisation/patient number according to his stratum from a block of randomisation numbers per site. The randomisation list will be generated by Haupt Pharma Brackenheim, Germany, using a validated system, which involves a pseudo-random number generator to ensure that the resulting treatment sequence will be both reproducible and non-predictable. Study medication will be packed and blinded by Haupt Pharma Brackenheim, Germany, according to the randomisation list. Each patient medication box will be sent together with the sealed unblinding codes to the sites. The

investigator at the site takes care that each patient will be provided with the study medication box of the correct randomisation number.

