## 8 STATISTICS

### 8.1 *Sample size and power considerations*

In four previous ALS trials in which the principal investigator was involved, the rate of loss to follow up was less than 1 % (Exonhit/Pentoxifyllin, ONO2506, 5000 mg Vitamin E trial, TCH346-Novartis-Trial). We expect to repeat this low rate, since ALS is a life threatening disease and the centres involved are experienced in the clinical care for the patients.

The study will be conducted using a two-stage group sequential test design within the  $\Delta$ -class of critical values according to Wang and Tsatis. The planned information rates are 0.5 and 1. These information rates fix the weights for combining the p-values using the weighted inverse normal method. The critical values of the group sequential test design were calculated for the standardised (cumulative) test statistic for the design with boundary shape parameter  $\Delta = 0.0$ , i.e. O'Brien/Fleming type design. For one-sided

$\alpha = 0.025$  and the information rates given above the resulting boundary p-values are given by  $p_1 = 0.00258$  and  $p_2 = 0.02400$  with corresponding critical values 2.797 and 1.977, respectively.

For one-sided  $\alpha = 0.025$  and 18-month survival rates of 60% in the standard group and 78% in the test group (hazard ratio = 0.486), the statistical power is 80% if the log-rank test is performed after observation of a total of 31 deaths at the first stage and after 61 deaths (accumulated number) at the second (final) stage (formula of Schoenfeld, ADDPLAN® version 3.1.2, ADDPLAN GmbH, Germany).

Assuming an accrual time of 6 months and a follow-up time of 15 months (21 months observation time) a total of 198 subjects (99 subjects per treatment group, without drop-outs) is expected to yield the necessary number of deaths if the accrual rate is constant (conservative estimation). Under these assumptions, the time points of analyses are expected to be 11.1 months observation time (interim analysis) and 21 months observation time (final analysis).

Thus, considering a drop-out rate of 10%, it is planned to enrol a total of 220 patients.

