### 8.2.8 Other evaluations

#### **Subgroup Analyses**

Subgroup analyses will be performed for the bulbar and spinal stratum.

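### The confirmatory log-rank test is written without the onset strata used in randomisation; adding them is a small, essentially free gain if onset is prognostic

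*Protocol*

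**What the plan says.** Protocol sections 1 and 5.1 describe a stratified trial, and section 6.10.1 defines the factor: "Patients will be assigned to the bulbar or spinal stratum according to the location of the earliest experienced ALS symptom". That section also covers simultaneous, cervical and respiratory onset, and issues randomisation numbers by stratum within site.

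Section 8.2.5 sets out the confirmatory procedure: one overall hazard ratio, a one-sided level of 0.025, critical values 2.797 and 1.977, an inverse normal combination and a repeated confidence interval. The test itself is given as "The null hypothesis will be tested using the log-rank test". No strata are named. Section 8.1 sizes the trial on the same test.

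The only analysis for which the protocol names onset is in section 8.2.8: "Subgroup analyses will be performed for the bulbar and spinal stratum".

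Section 8.2 leaves analysis details to a statistical analysis plan prepared by the study statistician. Section 8.2.7 adds a separate plan for the interim analysis, prepared by the unblinded statistician. Neither is at hand.

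**The concern.** Stratified randomisation balances the arms on onset. An analysis that leaves onset out does not benefit from that balance. If the two strata have different death rates, the unstratified log-rank statistic is less variable under the null hypothesis than its variance formula assumes, so the test is conservative. Its hazard ratio also mixes two risk groups and moves a little towards 1. Both effects reduce power on the only confirmatory endpoint.

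The design adds two reasons to settle the wording:

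- The final decision combines the two stages. The second-stage contribution is what the final statistic adds to the interim one, so both must be the same statistic. Two plans with two authors could read an unqualified reference to the log-rank test differently.
- Section 8.2.5 allows the number of deaths to be recalculated from the interim effect estimate, so the choice of estimator also enters that decision.

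**Working it through.** **1. The plan's own figures.** Section 8.1 assumes "18-month survival rates of 60% in the standard group and 78% in the test group (hazard ratio = 0.486").

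- Hazard ratio: ln(0.78)/ln(0.60) = 0.4864.
- Schoenfeld, 1:1 allocation: d = 4(1.960 + 0.842)²/(ln 0.4864)² = 60.4, rounded up to 61 deaths.
- Two-stage power: the expected log-rank statistic is √(d/4)·|ln HR|, which is 2.006 at 31 deaths and 2.815 at 61. With correlation √(31/61) and boundaries 2.797 and 1.977, power is 80.1%. Under the null hypothesis, at information rates 0.5 and 1, the overall level is 0.0250.
- Deaths expected with 99 per arm and uniform 6-month accrual: 30.7 at 11.1 months and 61.3 at 21 months.
- Enrolment: 198/0.90 = 220.

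All of these agree with the protocol.

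**2. Stratified against unstratified test.** The simulation used 198 patients, blocks of 4 within onset stratum, exponential survival, analyses at 31 and 61 deaths with the protocol's boundaries, cumulative log-rank statistics and no sample size adaptation. Control 18-month survival was held at 60%, with a treatment hazard ratio of 0.486 within each stratum. There were 20,000 trials per setting (Monte Carlo standard error about 0.3 points for power). The bulbar share (20, 30, 40%), the bulbar:spinal hazard ratio and the block size are assumptions; the protocol gives none of them.

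| Bulbar:spinal hazard ratio | Power, unstratified | Power, stratified | Gain (points) | One-sided size, unstratified | One-sided size, stratified |
|---|---|---|---|---|---|
| 1 | 78.4–79.3% | 78.4–79.1% | −0.2 to 0.0 | 0.025–0.026 | 0.024–0.026 |
| 1.5 | 78.2–78.4% | 78.4–78.6% | 0.2–0.3 | 0.024 | 0.025 |
| 2 | 77.3–78.0% | 78.4–78.8% | 0.8–1.4 | 0.023 | 0.023–0.025 |
| 3 | 75.0–75.7% | 78.3–78.7% | 2.9–3.4 | 0.020–0.021 | 0.024–0.026 |

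Ranges run over the three bulbar shares. A second simulation with 220 patients, 30% bulbar, 25,000 trials per setting and stage-wise increments combined with weights √0.5 agrees: 78.2% against 78.6% at ratio 1.5, 77.6% against 78.7% at 2, and 75.6% against 78.5% at 3.

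**3. In deaths.** Going from 60 to 61 deaths raises power from 79.42% to 80.07%, or 0.65 points per death. The loss is then worth 0.8/0.65 to 1.4/0.65, about 1 to 2 deaths, at ratio 2. At ratio 3 it is 2.9/0.65 to 3.4/0.65, about 5 deaths.

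**4. Attenuation of the hazard ratio.** With bulbar share p and ratio r, solve (1−p)e^(−18λ) + p·e^(−18λr) = 0.60 for the spinal control hazard λ. Then multiply both hazards by 0.4864 to get test-arm survival S. The overall 18-month cumulative-hazard ratio is ln(S)/ln(0.60). For p = 30%:

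- r = 1.5: S = 77.9%, ratio 0.489
- r = 2: S = 77.7%, ratio 0.494
- r = 3: S = 77.2%, ratio 0.508

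The shift from 0.486 is therefore at most about 0.02.

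**5. Why not by site.** With about 16 sites, 61/16 is roughly 4 deaths per site. Onset gives two strata only.

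**The case against.** The strongest reply is that the protocol nowhere says the test is unstratified. It names a family of tests for a trial that it calls stratified, and defers the details to an analysis plan that may well name the strata. That stands: the unstratified reading is the natural one of a sentence that lists no strata, but it comes from silence. It does not remove the point. Section 8.2.5 otherwise fixes the confirmatory procedure down to the critical values, and the form of the only confirmatory test belongs with them.

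A second reply is that nothing stated is wrong. That also stands. A reader might infer that the primary test is invalid, but leaving onset out makes it conservative, so the claim "This procedure preserves the overall (experiment-wise) type I error rate of" 0.025 is not threatened.

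A reader might also set a simulated 77.6% beside the planned 80% and put the whole gap down to stratification. The documents do not support that. With no prognostic difference both tests already sit at about 78 to 79%, because the Schoenfeld approximation is mildly optimistic at this hazard ratio. The simulations also place 0.486 within strata, while section 8.1 derives it from overall survival, so the test arm falls slightly short of 78% once onset is prognostic. Only the difference between the two tests on the same simulated data measures the effect of stratifying.

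Finally, the hazard-ratio shift is the difference between an overall and a within-stratum quantity. It is not a bias in the overall ratio that section 8.2.5 defines.

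**Conclusion.** The point holds as a small, conditional loss of efficiency. As written, the confirmatory test does not use the factor on which randomisation was stratified. The cost depends on how strongly onset predicts death, for which the protocol gives no figure. Over bulbar shares of 20 to 40% it is nil at a bulbar:spinal hazard ratio of 1, under half a point at 1.5, about 1 point at 2 and about 3 points at 3. The required 61 deaths, the boundaries and the type I error control are all sound. A general finding that the trial is underpowered, or that the protocol prescribes an unstratified test, would go beyond the text. The change is worth making because stratifying costs at most about 0.2 points when onset is not prognostic, and because one explicit wording keeps the interim and final analyses on the same statistic.

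**What to change.** Before the interim analysis, amend section 8.2.5 to say that the log-rank statistic at both stages is stratified by randomisation stratum (bulbar, spinal onset) and not by site. Take the hazard ratio and its repeated confidence interval from the matching stratified model, and keep the unstratified log-rank test as a sensitivity analysis. Put the same wording in the interim and final analysis plans. If a plan already names the strata, bring the protocol sentence into line with it.

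The cost is a sentence or two in each document. The stratum is assigned for every randomised patient, and the number of deaths, the boundaries, the enrolment and the data collection stay as they are.

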#### **4.3.1 Inclusion criteria**

To be considered eligible to participate in this trial a patient must meet the inclusion criteria listed below.

- Possible, probable (clinically or laboratory) or definite ALS according to the revised version of the El Escorial World Federation of Neurology criteria
- Disease duration more than 6 months and less than 3 years (inclusive). Disease onset defined as date of first muscle weakness, excluding fasciculation and cramps
- Best-sitting SVC between 50 % and 95 % of predicted normal
- Continuously treated with 100 mg riluzole daily, for at least 3 months
- Capable of thoroughly understanding all information given and giving full informed consent according to GCP
- Women of childbearing age must be non-lactating and surgically sterile or using a highly effective method of birth control and have a negative pregnancy test. Acceptable methods of birth control with a low failure rate i.e. less than 1% per year) when used consistently and correct are such as implants, injectables, combined oral contraceptives, hormonal intrauterine devices (IUDs), or double-barrier methods (condom or diaphragm with spermicidal agent or IUD), sexual abstinence or vasectomised partner.
- Onset of progressive weakness within 36 months prior to study

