### **Screening Visit (V0)**

A signed "Informed Consent" will be obtained from each patient prior to initiating any trial procedure. Presence of ALS diagnostic criteria will be documented as well as site of onset and ALS status at entry according to El Escorial criteria, and modified by the Airlie House criteria (<http://www.wfnals.org>). Venous blood will be taken for the determination of blood cell count, creatinine, CK, ASAT, ALAT, fasting blood glucose, and HCG or urine pregnancy test (only in women with child bearing potential). The patients' eligibility will be determined in accordance with the inclusion/exclusion criteria. A detailed medical history will be taken, and concomitant medication will be recorded. A physical examination, including body weight, height, blood pressure, and radial pulse will be performed. Additionally lung function will be assessed by measuring the patient's vital capacity.

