### **Visit 1 – Baseline visit (V1)**

Patients eligible for study participation will enter the study site within 4 weeks after the screening visit and will be randomised to one of the treatment arms.

Blood samples for the determination of blood cell count, creatinine, CK, ASAT, ALAT, fasting blood glucose, and pioglitazone baseline level will be obtained. A physical examination, ALS FRS-R, and EuroQol EQ-5D will be performed. The patient will receive study medication according to the randomization list and a study participant card (see appendix IX).

Any changes in the concomitant medication and adverse events before and during visit 1 will be documented.

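### The only confirmatory analysis is an unadjusted log-rank test although three baseline disease measures are recorded on every patient; adjusting for them would change power by about -1 to +11 points, depending on how prognostic they are

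*Protocol*

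**What the plan says.** Protocol section 8.2.5 sets the confirmatory test in one sentence: "The null hypothesis will be tested using the log-rank test". For estimation, "the hazard ratio and the corresponding two-sided 95% repeated confidence interval will be provided". Section 8.1 powers the trial for the same test in a two-stage O'Brien/Fleming type design: "The planned information rates are 0.5 and 1", "with corresponding critical values 2.797 and 1.977, respectively", for one-sided alpha 0.025. Neither section names a covariate or a stratification factor, and 8.2.5 treats all other group comparisons as exploratory. Onset site, the randomisation stratum in 6.10.1, returns in the analysis only as a subgroup (8.2.8).

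The baseline information is already collected. At screening: "Additionally lung function will be assessed by measuring the patient's vital capacity". At baseline: "A physical examination, ALS FRS-R, and EuroQol EQ-5D will be performed". Section 4.3.1 requires the date of onset, because disease duration must lie between 6 months and 3 years, and it limits vital capacity to 50-95% of predicted. None of the three measures has a role in the primary analysis.

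**The concern.** Patients within each arm differ in disease stage at entry. If those differences predict death, a test that ignores them is less sensitive than one that uses them. The hazard ratio averaged over unlike patients then lies closer to 1 than the ratio between like patients.

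The whole trial rests on 61 deaths, so efficiency matters. Chance imbalance in disease stage also enters the estimate uncorrected. Section 8.2.2 looks for such imbalances, but no confirmatory analysis takes account of them. At the interim the standard error of the log hazard ratio is already about 2/√31 = 0.36, and 8.2.5 lets the number of deaths be recalculated from that estimate.

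**Working it through.** **Step 1: the protocol's own figures (8.1).**
- Hazard ratio: ln(0.78)/ln(0.60) = 0.2485/0.5108 = 0.486, as stated.
- Drift (Schoenfeld): √(61/4) × |ln 0.486| = 3.905 × 0.7215 = 2.818. With boundaries 2.797 and 1.977 at information 0.5 and 1, overall alpha is 0.0250 and two-stage power is 80.2% (stated 80%).
- Expected deaths in 198 patients (exponential survival, uniform 6-month accrual): 30.7 at 11.1 months and 61.3 at 21 months. The stated targets are 31 and 61.
- Enrolment: 198/0.9 = 220.

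Everything reproduces.

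**Step 2: what adjustment would change.** The protocol gives no prognostic strength, so it is an assumption here. The three covariates are combined into a score whose log-hazard SD is s. For three equal, independent covariates, the hazard ratio per SD of each is exp(s/√3): 1.33 at s = 0.5 and 1.78 at s = 1.0.

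The two-stage trial was simulated with 198 patients, looks at 31 and 61 deaths, and boundaries 2.797 and 1.977. The 60% and 78% were kept as the marginal 18-month survival rates. Cumulative statistics were used, which equal the inverse normal statistic when the sample size is not adapted. Three sets of runs:
- A: Cox model with the three covariates, unstratified, 10,000 runs per scenario.
- B: the same, stratified by onset (30% bulbar and no onset effect assumed), 6,500 runs.
- C: stratified by onset, 3,000 runs per scenario.

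Overall power, log-rank v adjusted (%):

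| Log-hazard SD | A | B | C | Change (points) |
|---|---|---|---|---|
| 0 (0.01 in A) | 78.2 v 76.8 | 79.0 v 77.4 | 79.5 v 78.6 | -0.9 to -1.6 |
| 0.3 | 78.6 v 78.8 | 79.1 v 78.8 | 80.3 v 80.0 | -0.3 to +0.2 |
| 0.5 | 79.4 v 81.7 | 78.4 v 80.2 | 80.2 v 82.5 | +1.8 to +2.3 |
| 0.8 | 79.3 v 86.3 | not run | 80.2 v 86.8 | +6.6 to +7.0 |
| 1.0 | 79.8 v 90.6 | not run | 80.6 v 90.8 | +10.2 to +10.8 |

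The simulation error of a single power figure is √(0.8 × 0.2/n): 0.4 points in A, 0.5 in B and 0.7 in C.

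**Step 3: scale in deaths.** In a fixed design, the deaths needed are proportional to (1.960 + z for power)². At SD 0.5 (set A) the ratio is (1.960 + 0.904)²/(1.960 + 0.820)² = 1.06, or about 4 deaths on 61. At SD 0.8 it is (1.960 + 1.094)²/(1.960 + 0.817)² = 1.21, or about 13 deaths.

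**Step 4: the interim boundary.** Probability of crossing 2.797 at 31 deaths, log-rank v stratified and adjusted:
- SD 0: 19.3% v 15.0% (B) and 19.0% v 14.0% (C).
- SD 0.3: 19.4% v 15.3% (B).
- SD 0.5: 20.9% v 17.3% (B) and 20.8% v 18.2% (C).

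**Step 5: type I error.** With no treatment effect and 4,000 runs, the unstratified adjusted test rejected in 2.1% (SD 0.5) and 2.9% (SD 0.8), against 2.4% and 3.0% for the log-rank test. The simulation error is √(0.025 × 0.975/4000) = 0.25 points, so these runs show no clear inflation from adjusting.

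**The case against.** The strongest reply is that nothing here is wrong. The protocol powers the trial for a log-rank test and then uses it. In the table its power stays near 80% however prognostic the covariates are. That stands, and it rules out two stronger readings.

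A reader might infer that the trial is underpowered or that 80% is overstated. That would follow if 0.486 were the hazard ratio between patients with the same covariates: unadjusted power would then be 74.7%, 70.4% and 63.4% at SD 0.5, 0.8 and 1.0. But 8.1 derives 0.486 from the 18-month survival of whole groups, which is the marginal reading.

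A reader might also infer a definite loss of several points. The documents support no definite figure. The change is nil at SD 0.3 and negative at SD 0. The limits on vital capacity and duration in 4.3.1, and correlation among the covariates, push any gain down.

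Three further objections stand as limits on the remedy:
- It lowers the chance of early stopping for superiority, which 7.6.2 provides for, when the covariates are weak to moderate.
- Vital capacity is FVC in the trial summary and SVC in 4.3.1, so the covariate is not yet defined.
- Section 8.3 does not replace missing baseline data, so without a rule a patient lacking a covariate would drop out of the confirmatory model.

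It can also be said that adjusted analyses belong in the SAP. For a supportive analysis that is right, and its absence from the protocol is no finding. It does not settle the confirmatory test, which 8.2.5 itself fixes.

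**Conclusion.** The point holds as a missed opportunity in an otherwise sound primary analysis. The log-rank test is valid and its stated power is correct. Adjusting for three measures already collected would change overall power by about -1 (at worst -1.6), 0, +2, +7, or +10 to +11 points at an assumed log-hazard SD of 0, 0.3, 0.5, 0.8 or 1.0. The figures assume proportional hazards, normally distributed independent covariates and the protocol's marginal survival rates. The likelier direction of departure from those conditions is towards smaller gains. The trade is still favourable if the covariates are at least moderately prognostic, and the loss is small if they are not. It is a cheap improvement worth making, not a correction that the trial's validity depends on.

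**What to change.** In 8.2.5, base the stage-wise statistics and the hazard ratio on the treatment effect from a Cox model stratified by onset site. Enter as linear covariates screening vital capacity (% predicted), baseline ALSFRS-R total and disease duration. For vital capacity, use the measure named in 4.3.1 once the FVC in the summary and the SVC there are reconciled. Fix the model before the interim analysis, with a simple pre-stated rule that keeps patients with a missing covariate in the analysis. Keep the inverse normal weights and the critical values 2.797 and 1.977, and report the log-rank test as a sensitivity analysis.

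The change is one of wording and needs no new data or patients. Its costs should be stated with it:
- about 1 to 2 points of power if the covariates are not prognostic;
- a lower chance of crossing the boundary at 31 deaths (about 19% to 14-15% at SD 0, about 21% to 17-18% at SD 0.5);
- a hazard ratio that is conditional on the covariates and must be reported as such.
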